### Randomisation and blinding

Randomisation is computerised using CastorEDC [26], an Electronic Data Capture program complying with all regulatory guidance [27]. Participants are allocated using a 1:1 randomisation ratio scheme. Randomisation is stratified for hospital, sex and type of IBD. In order to ensure balanced groups, block randomisation with block sizes of either 2, 4 or 6 are used. Participants cannot be blinded to allocation. For reasons of coordination and logistics, randomisation is performed by a member of the research team, and the research team has therefore access to the information about the assigned group.

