### Intervention: MBCT

The MBCT program is based on the protocol published by Segal, Williams and Teasdale [14]. The program consists of eight weekly 2.5 hour sessions, a six hour silent day between session 6 and 7, and daily home practice of 45 minutes guided by audio files. Groups consist of eight to ten participants. Materials are adjusted to include IBD-related examples. The course is offered in the cities where patients are treated (Nijmegen, Arnhem and ‘s-Hertogenbosch) and taught by qualified teachers according to the advanced criteria of the Association of Mindfulness-Based Teachers in the Netherlands and Flanders [28]. These criteria include a minimum of 150 hours of education in MBSR/MBCT (entailing theoretical background, skills practice, supervision and reflection), a minimum of three years of personal meditation practice and attending retreats, and providing a minimum of two courses per two years. All mindfulness teachers participated in a kick-off meeting before the start of the trial, in which the trial-specific MBCT protocol was discussed. Peer supervision meetings are organised twice per MBCT course during the intervention phase of the trial. Teaching sessions are recorded and a random sample of sessions will be rated by two independent raters using the Mindfulness-Based Interventions: Teaching Assessment Criteria (MBI:TAC) [29]. Participation of the training can be discontinued on participant’s request at any time. If so, the participant is encouraged to complete further assessments of the study.

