### Comparator: treatment as usual

TAU consists of all healthcare that patients usually receive to treat IBD according to Dutch and European treatment guidelines [30–33]. These treatments mainly focus on pharmacological and surgical disease control and prevention of complications. TAU can also include non-mindfulness based psychosocial treatments. All healthcare use is registered (see outcome measures, cost-effectiveness). After the final assessment, participants of the TAU group will also be given the opportunity to participate in an MBCT course.

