#### Treatment effects at post-treatment: primary outcome

All analyses will be performed and reported according to the CONSORT guidelines, i.e. primarily on intention-to-treat basis. Treatment effects on the primary outcome (psychological distress at post-treatment, assessed with the HADS) will be analysed using Linear Mixed Effect models, with time, group (MBCT + TAU versus TAU) and Group*Time interaction effects added as fixed effects, while controlling for baseline HADS score and stratification variables (i.e. centre, sex, IBD type). To account for possible dependency caused by clustering in intervention groups, we will add ‘group’ as a random effect if the intra-cluster correlation ≥ 0.05. Restricted maximum likelihood will be used as estimation method to handle missing data. Effect sizes will be calculated using Cohen’s *d*, with values of 0.20–0.50 indicating small effects, 0.50–0.80 moderate effects, and > 0.80 large effects [73]. Cohen’s *d* will be calculated by dividing the adjusted group difference between the means at T1 by the pooled standard deviation at T0.

We will also perform a per-protocol analysis selecting all participants who completed at least half of the MBCT sessions (4 or more) for those assigned to the MBCT condition and inversely, all who have not participated in any mindfulness intervention for those assigned to the TAU condition.

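### The supplementary per-protocol analysis selects on session attendance in the MBCT arm only, so its two sets are not comparable; a complier-average estimate beside the ITT result would answer the same question without that selection.

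*Protocol article*

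**What the plan says.** All of this is in the protocol article. Under the heading on post-treatment effects for the primary outcome, analyses are "primarily on intention-to-treat basis". The HADS model has time, group and their interaction, "while controlling for baseline HADS score and stratification variables (i.e. centre, sex, IBD type".

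The same section then adds: "We will also perform a per-protocol analysis". The rule differs by arm:

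- MBCT arm: "selecting all participants who completed at least half of the MBCT sessions (4 or more) for those assigned to the MBCT condition". The intervention section gives the denominator: "The program consists of eight weekly 2.5 hour sessions".
- TAU arm: "all who have not participated in any mindfulness intervention for those assigned to the TAU condition". The comparator section allows other psychological care: "TAU can also include non-mindfulness based psychosocial treatments".

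The text on this analysis names no adjustment for what drives attendance and no estimator that compares like with like.

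**The concern.** Randomisation makes the full arms comparable; it does not do so for subsets chosen by later behaviour. Each arm contains patients who would attend 4 or more sessions if offered MBCT and patients who would not. The rule removes the second kind from the MBCT arm. In TAU nobody was offered sessions, so those patients cannot be identified and remain. The TAU filter concerns contamination, which is a different behaviour, and does not mirror the attendance filter.

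If patients who attend little would have had higher HADS scores anyway, for reasons not captured by baseline HADS, centre, sex and IBD type, their one-sided removal lowers the MBCT mean and looks like benefit. This is the only planned analysis of the primary outcome by treatment received. Its result matters most if the ITT estimate is weak and the per-protocol estimate is positive. A reader could then conclude that MBCT works for those who attend, when selection alone can give that pattern.

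**Working it through.** **Inputs from the article.** Planned effect d = 0.51; 98 patients before dropout (49 per arm); 136 after (68 per arm). The dropout step reproduces: (11.5 + 44)/2 = 27.75, rounded to 28%, and 98/(1 − 0.28) = 136.1. The article gives no figure for the per-protocol analysis itself.

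**Assumed inputs.** True effect zero; share q of the MBCT arm below 4 sessions, 20 to 40%; such patients score g = 0.3 to 0.5 SD worse in either arm after covariate adjustment. Lower HADS is better, so a negative contrast favours MBCT.

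**Bias.** The TAU mean contains q × g from its would-be non-attenders and the selected MBCT mean contains none. The expected contrast is therefore −q × g.

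**Rejection rate at two-sided 5%.** With 49 in TAU and 49(1 − q) in MBCT, SE = √(1/49 + 1/[49(1 − q)]) and z = q × g/SE. The rate is about P(Z > 1.96 − z) + P(Z < −1.96 − z).

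| q | g (SD) | Contrast (SD) | MBCT n | SE | z | Rejection, approximation | Rejection, simulation |
|---|---|---|---|---|---|---|---|
| 0.20 | 0.3 | −0.06 | 39.2 | 0.214 | 0.28 | 6% | 5% |
| 0.30 | 0.5 | −0.15 | 34.3 | 0.223 | 0.67 | 10% | 10% |
| 0.40 | 0.5 | −0.20 | 29.4 | 0.233 | 0.86 | 14% | 13% |

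The simulation used 4,000 trials per setting; its mean ITT and complier-average estimates were within 0.012 SD of zero. The middle row is 0.15/0.51 = 29% of the planned effect. The first row shows hardly any inflation.

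**Second parametrisation.** Here there are 68 per arm, a baseline–outcome correlation of 0.5, and attendance propensity correlated r with better outcome beyond baseline. Cell entries are mean contrast in SD and rejection rate.

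| Share below 4 sessions | r = 0 | r = 0.2 | r = 0.3 | r = 0.5 |
|---|---|---|---|---|
| 11.5% | 0.00, 4.6% | −0.04, 5.6% | −0.06, 6.9% | −0.10, 9.5% |
| 28% | 0.00, 4.5% | −0.08, 7.8% | −0.12, 10.8% | −0.20, 23.6% |
| 44% | 0.00, 5.2% | −0.12, 10.7% | −0.18, 17.4% | −0.31, 44.9% |

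ITT on the same data rejected 4.5 to 5.8% of the time. The shares borrow the article's dropout figures as illustrative values only. With r = 0 there is no bias; a negative r would reverse the sign.

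**Does the TAU filter compensate?** At 28% and r = 0.3, also removing 5% of TAU gives −0.12 SD and 11.0% if removal is unrelated to outcome. It gives −0.09 SD and 9.0% if those removed are worse off. The bias shrinks somewhat in the second case but stays.

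**The alternative.** The complier-average effect is the ITT difference divided by the difference between arms in the proportion exposed. With 70% exposed in MBCT and none in TAU it is ITT/0.70, and the interval widens by about 1/0.70 = 1.43. At 80% and 60% exposed the factors are 1.25 and 1.67.

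**The case against.** The strongest reply is that ITT is primary, the per-protocol analysis is only additional, and no conclusion in the article is tied to it. The 4-session threshold is fixed in advance, and such a set beside ITT is conventional. Interpretive cautions and further estimators often sit in the full protocol or analysis plan, which are not shown. All of this limits the weight of the point. It does not make the stated contrast unbiased, because the selection rule itself is written into the article.

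Three stronger readings are tempting, and the article does not support them:

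- A reader might infer that attenders are compared with an unselected TAU arm. TAU is filtered too, on mindfulness participation; what is missing is selection on attendance.
- A reader might take 28% and 44% as non-attendance rates. They are trial dropout rates used to inflate the sample size, and the intervention section asks patients who stop the training to continue assessments. Moreover, 49 per arm is already net of dropout. If many poor attenders are also dropouts, the share left to exclude is smaller: at an illustrative 10% the bias is 0.10 × 0.3 to 0.10 × 0.5, or 0.03 to 0.05 SD.
- A reader might infer that the bias must favour MBCT. That is plausible, but the article reports nothing on who attends.

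The remedy can also be challenged. A complier-average estimate assumes that assignment itself, and fewer than 4 sessions with home practice, have no effect. That is debatable here, since "Participants cannot be blinded to allocation" and the HADS is self-reported. With little crossover the estimate is also largely a rescaled ITT result. Both points stand. The assumption should be stated and checked, and the rescaling is what ties the estimate to the randomised comparison.

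**Conclusion.** The point holds for the supplementary analysis only. The per-protocol contrast compares sets selected by different post-randomisation behaviours, and the covariates in the model remove the resulting bias only if they capture everything that links attendance to outcome. It does not follow that the trial's primary conclusion is at risk; the ITT analysis is untouched.

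The size is conditional. Under 20 to 40% non-attendance and a 0.3 to 0.5 SD worse prognosis, a null effect appears as about −0.06 to −0.20 SD, with 5 to 13% false positives. The article supplies neither input. The bias can be nil, smaller than this, larger under a stronger link, or opposite in sign. It is worth correcting because the change is cheap and the result is otherwise easy to over-read.

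**What to change.** Keep ITT as primary. Beside it:

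- Estimate the effect in attenders as a complier-average causal effect on HADS at 3 months, with randomised arm as the instrument for attending at least 4 sessions, adjusted for baseline HADS, centre, sex and IBD type.
- Count mindfulness participation in TAU as exposure in that model instead of excluding those patients. The present TAU rule already requires this information. For illustration, 70% exposed in MBCT and 5% in TAU would give ITT/0.65.
- State the assumption that assignment and fewer than 4 sessions have no effect of their own, and repeat the estimate with a lower attendance threshold.
- Report the per-protocol contrast as non-randomised and descriptive, without a test-based claim.

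The cost is a few lines of plan and one extra model. Attendance and TAU exposure are already needed for the planned set, and patients who stop the training are encouraged to stay in follow-up, so no new data collection is needed. The price is a wider interval and reliance on the exclusion assumption.

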#### Treatment effects at post-treatment: secondary outcomes

Treatment effects on the secondary outcomes (subjective sleep quality (PSQI, ISI), fatigue (FACIT-F), IBD-related QoL (SIBQ), perceived control over IBD (IBD-control), disease activity (HBI, SCCAI, laboratory results), repetitive negative thinking (PTQ), mindfulness skills (FFMQ-SF), self-compassion (SCS-SF), positive mental health (MHC-SF, FACIT-F QoL domains) and objective sleep parameters: TST, SE, SOL, WASO, relative and absolute duration of REM, and relative and absolute duration of deep sleep at post-treatment will be analysed using separate Linear Mixed Effect models, with time, group (MBCT + TAU versus TAU) and Group*Time interaction effects added as fixed effects, while controlling for baseline score of the variable of interest and stratification variables (i.e. centre, sex, IBD type). The same parameters as in the primary analysis will be used for these analyses. In addition, we will use regression analyses to investigate whether more mindfulness practice (MAQ) is also associated with better outcomes.

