### Procedure and assessments

Figure 1 provides a flowchart of the study procedure. In order to minimize the risk of selection bias by attending physicians, all IBD patients treated in these hospitals receive an invitation leaflet. Those interested in participation are referred to an online, anonymous pre-screening survey [25], which includes the HADS and questions about the main eligibility criteria. Probably eligible participants are guided to a registration form, after which they receive additional information about the trial and are invited for a research interview. During this research interview the study is explained in more detail, the inclusion and exclusion criteria are reviewed thoroughly and written informed consent is obtained (Appendix 1). Definite eligibility is determined after laboratory screening to rule out anaemia or elevated faecal calprotectin levels. After definite inclusion in the study, participants are invited for the baseline assessment, which consists of: (1) self-report questionnaires; (2) an interview in which demographic and disease characteristics are examined (age, sex, country of origin, level of education, marital status, employment status, body mass index, IBD type, medication use, age at onset of IBD, time since last flare, hospitalizations due to flare, comorbid psychiatric diagnoses); and (3) sleep analysis, using sleep electroencephalography (EEG) headband for three consecutive nights. From baseline until post-treatment, participants are asked to wear an actigraphy wristband for additional sleep data. At post-treatment, they are asked to sleep another three nights with the EEG headband. The post-treatment assessment (3 months after baseline) and the follow-up assessments (6, 9 and 12 months after baseline) consist of self-report questionnaires and an interview by clinician. The 6- and 12-month assessments include blood and stool samples for all participants. The 3- and 9-month assessment includes blood and stool samples only for patients with a suspected flare. Table 1 provides an overview of assessments and measures. The content of the outcome measures is explained below under the heading ‘outcome measures’.

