Laboratory tests will be performed every 6 months (T0, T2 and T4), following the regular medical check-ups [54] and extra in case a flare is suspected (HBI ≥ 5, SCCAI ≥ 3). These tests consist of faecal calprotectin, haemoglobin, C-reactive protein and albumin. Having higher levels of faecal calprotectin and C-reactive protein plus low albumin may indicate disease activity [54–56].

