#### Treatment effects at follow-up

In order to investigate consolidation of the treatment effects over time on both the primary outcome (psychological distress) and secondary outcomes (all secondary outcomes except objective sleep parameters) we will again perform linear mixed effect models with time (T1, T2, T3, T4), group (MBCT + TAU versus TAU) and Group*Time interaction, including the same parameters as mentioned above and controlling for baseline levels and stratification variables. Restricted maximum likelihood will be used as estimation method to handle missing data. Cohen’s *d* will be calculated by dividing the adjusted group difference between the means at T4 by the pooled standard deviation at T0.

We also aim to examine the effect of MBCT on recurrence of disease activity (flares). Therefore, we will perform a proportional hazards model (i.e. Cox regression analysis) to analyse the differences between MBCT + TAU and TAU alone in time to flare within the 12-months study period.

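### Laboratory results are to be analysed at 3 months (T1) and over T1–T4, but at T1 and T3 blood and stool are taken only when a flare is suspected

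*Protocol article*

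**What the plan says.** Four places in the Protocol article bear on this.

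- **Analysis at post-treatment.** The section on post-treatment effects for secondary outcomes includes "disease activity (HBI, SCCAI, laboratory results), repetitive negative thinking (PTQ" in a list of outcomes that "at post-treatment will be analysed using separate Linear Mixed Effect models". The models adjust for the baseline value of the outcome, centre, sex and IBD type.
- **What post-treatment means.** Procedure and assessments fixes it: "The post-treatment assessment (3 months after baseline", that is, T1.
- **When samples are taken.** The same section states: "The 3- and 9-month assessment includes blood and stool samples only for patients with a suspected flare". By contrast, "The 6- and 12-month assessments include blood and stool samples for all participants". The laboratory paragraph under IBD-related measures agrees: "Laboratory tests will be performed every 6 months (T0, T2 and T4"), and "extra in case a flare is suspected (HBI ≥ 5, SCCAI ≥ 3"). Table 1 puts the T1 and T3 ticks for blood tests and faecal calprotectin in brackets.
- **Analysis at follow-up.** Treatment effects at follow-up applies a mixed model with time levels T1, T2, T3 and T4 to the "secondary outcomes (all secondary outcomes except objective sleep parameters"). Objective sleep is taken out of that model; laboratory results are not. REML is the only provision for missing data.

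**The concern.** The analysis sections treat laboratory values as if everyone had them at T1 and T3. The sampling schedule says otherwise, and what decides whether a T1 or T3 sample exists is the patient's own HBI or SCCAI score at that visit.

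That score is measured after randomisation, is itself an analysed outcome, and is not a term in the laboratory model. Two consequences follow.

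1. The T1 laboratory contrast compares suspected-flare patients in one arm with suspected-flare patients in the other, not the groups as randomised. If MBCT changes symptom scores, the arms are selected differently. The trial is open-label, and both indices score general well-being.
2. In the T1–T4 model, the observed T1 and T3 values come from suspected flares and those at T2 and T4 from everyone. The time course is distorted even if the treatment does nothing.

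At stake is a 3-month laboratory effect that would be reported on an intention-to-treat basis although the design cannot supply it.

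**Working it through.** **Step 1. Schedule against analysis, for laboratory results**

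| Visit | Who is sampled | Used in post-treatment model | Used in follow-up model |
|---|---|---|---|
| T0 | everyone | as covariate | as covariate |
| T1 (3 months) | suspected flare only | yes | yes |
| T2 (6 months) | everyone | no | yes |
| T3 (9 months) | suspected flare only | no | yes |
| T4 (12 months) | everyone | no | yes |

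The post-treatment model uses the visit with selective sampling and neither of the follow-up visits at which everyone is sampled. Nothing in the article exempts laboratory results.

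**Step 2. How many might be sampled at T1**

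The article gives no 3-month rate of suspected flare. Its Background gives 5-year cumulative flare rates of 69–93% for Crohn's disease and 78–82% for ulcerative colitis. Assuming a constant hazard over 20 quarters:

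- 69%: 1 − 0.31^(1/20) = 0.057
- 93%: 1 − 0.07^(1/20) = 0.125
- The colitis rates fall between: 0.073 and 0.082.

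Of 136 randomised, that is about 8 to 17 patients with a flare in 3 months, both arms together. Suspected flares may be more frequent than true ones, so I take 10–30% as a working range. With the plan's 28% dropout, 68 × 0.72 = 49 per arm remain, of whom about 5, 10 or 15 would have a T1 sample at 10%, 20% or 30%.

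**Step 3. Precision**

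For an assumed true difference of 0.5 SD, two-sided 0.05, power ≈ Φ(0.5·√(n/2) − 1.96):

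| n per arm | Power |
|---|---|
| 4.9 | 12% |
| 9.8 | 20% |
| 14.7 | 27% |
| 49 (everyone) | 70% |

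**Step 4. Shift of the sampled mean**

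Let symptom score S and laboratory value Y be standard normal with correlation ρ, and let a sample be taken if S > c, where P(S > c) = p in TAU. Then E[Y | sampled] = ρ·λ(c), with λ(c) = φ(c)/(1 − Φ(c)).

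- p = 0.30: c = 0.524, λ = 1.159. With ρ = 0.3, shift = 0.35 SD.
- p = 0.10: c = 1.282, λ = 1.755. With ρ = 0.5, shift = 0.88 SD.

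This is how far observed TAU means at T1 and T3 would sit above the full-group mean with no real change over time. It needs no treatment effect.

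**Step 5. Between-arm bias at T1**

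If MBCT lowers S by δ and leaves Y unchanged, the sampled difference (MBCT − TAU) is ρ·[λ(c + δ) − λ(c)].

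- Smallest case (p = 0.30, δ = 0.3, ρ = 0.3): 0.3 × (1.386 − 1.159) = +0.07 SD
- Largest case (p = 0.10, δ = 0.5, ρ = 0.5): 0.5 × (2.181 − 1.755) = +0.21 SD
- δ = 0: zero

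A positive sign means that MBCT looks more inflamed.

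**Step 6. Bias against noise**

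Take p = 0.20 and ρ = 0.4. With δ = 0.3–0.5, MBCT sampling falls to 12.7–9.0%. Of 68 per arm, that is about 14 TAU against 9–6 MBCT patients. The bias is +0.10 to +0.16 SD. With a within-group SD near 0.93, the standard error is about 0.93·√(1/14 + 1/9) = 0.40 to 0.93·√(1/14 + 1/6) = 0.45 SD. The bias is about a quarter to a third of one standard error.

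**The case against.** The strongest reply is that little depends on this. It concerns one component of one secondary domain. The primary outcome, HADS at T1, is untouched. HBI and SCCAI are collected from everyone at every visit. The follow-up effect size is taken at T4, where everyone is sampled, and flares have their own Cox analysis. All of this stands and limits the weight of the point.

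The second reply is that the between-arm bias is hypothetical. That also stands. No input to Steps 4–6 for the trigger rate, the correlation or the symptom shift comes from the article. The planning effect of d = 0.51 is for psychological distress. On disease, the Background reports no difference in course in one MBSR trial and a non-significant improvement in activity in one MBCT trial. HBI and SCCAI are also clinician-based, not pure self-report.

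The third reply is that a likelihood-based model for T1–T4 borrows from the same patients' T2 and T4 values and the baseline covariate. That gives partial correction in the follow-up model. It does not give full correction, because the score that triggers sampling is absent from the model. The T1-only model has only the baseline value and the stratification factors to work with.

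A reader might infer that most T1 values, say over 80%, are missing by design, or that the T1 contrast is certainly biased between arms. The article supports neither. It gives no trigger rate, so 80% would only restate an assumed 20%. A small subset is likely given remission at entry, but remission is defined by calprotectin, and distressed patients may reach the symptom thresholds more often. If MBCT leaves symptom scores unchanged, the between-arm bias is about zero.

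**Conclusion.** The mismatch is real and is explicit in the article: laboratory results are assigned to analyses at visits where only patients with a suspected flare are sampled. As written, the T1 laboratory estimate describes a selected subset, and the T1 and T3 means are not on the same footing as T2 and T4.

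Two parts hold without any treatment effect on symptoms: the poor precision (power of roughly 12–27% instead of 70% under the assumptions of Steps 2–3) and the raised T1 and T3 means (about 0.35–0.88 SD). The between-arm bias of +0.07 to +0.21 SD is conditional on MBCT lowering symptom scores. It would run against MBCT, and in the worked case it is small beside its standard error. All these sizes are illustrative.

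This is a correction to a secondary outcome. It does not threaten the trial's main conclusion, and it leaves HBI, SCCAI and the laboratory sampling at T2 and T4 intact.

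**What to change.** - In the section on post-treatment effects for secondary outcomes, remove laboratory results from the T1 analysis. HBI and SCCAI stay.
- In Treatment effects at follow-up, restrict the laboratory model to T2 and T4, adjusted for the T0 value and the stratification factors.
- State that for-cause samples at T1 and T3 serve only to classify flares.

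The change is to wording only; no visit, sample or sample size changes. The cost is the loss of the nominal 3-month laboratory estimate, which the sampling schedule cannot support.
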